## Study procedures

### Participants

#### Diagnostic criteria

The diagnosis of NAFLD is according to the “Guidelines of prevention and treatment for nonalcoholic fatty liver disease (2018, China)” promulgated by the National Workshop on Fatty Liver and Alcoholic Liver Disease, Chinese Society of Hepatology, Chinese Medical Association [30]. In this trial, NAFLD participants are characterized by histopathology-proven significant hepatic steatosis or imaging-proven fatty liver by MRI-PDFF (MRI-PDFF>5%), and no history of alcohol or overconsumption (<210 g per week in men and <140 g per week in women during the past 12 months). Liver biopsy is difficult in the NAFLD clinic, recommend to participants to attempt biopsy to determine NASH status based on a voluntary principle or a medical indication.

The diagnosis of TCM syndromes is based on the “Diagnostics of Traditional Chinese Medicine” [31] and the “Consensus opinion on diagnosis and treatment of nonalcoholic fatty liver disease with integrated traditional Chinese and Western Medicine” [32].

#### Inclusion criteria

We will include eligible participants: ① diagnosed with NAFLD; ② aged 18 to 65 years; ③ with imaging evidence of liver MRI-PDFF ≥ 5%; ④ BMI < 35 kg/m^2^; ⑤ willing to follow the scheduled visit plan; ⑥ with serum alanine aminotransferase (ALT) < 5 times the upper normal limit (ULN); and ⑦ and signed informed consent.

#### Exclusion criteria

We will exclude those who: ① regularly took other hepatoprotective drugs within 1 month before screening; ② have taken drugs that may affect lipid metabolism within 3 months before screening, such as tamoxifen, amiodarone, sodium valproate, methotrexate, and glucocorticoid; ③ combined with special conditions that may lead to fatty liver, such as total parenteral nutrition, inflammatory bowel disease, celiac disease, hypothyroidism, Cushing’s syndrome, β-lipoprotein deficiency, lipoatrophic diabetes, and Mauriac syndrome; ④ are diagnosed of ALD (male alcohol intake > 30g/day, female alcohol intake > 20g/day), liver cirrhosis, liver decompensation, and other chronic liver diseases, such as hepatitis B, hepatitis C, autoimmune liver diseases; ⑤ have received liver transplantation; ⑥ combined with unstable controlled type 2 diabetes (HbA1c≥9.5% before enrolment); ⑦ combined with a high or extremely high risk of arteriosclerotic cardiovascular disease (ASCVD); ⑧ have had bariatric surgery in the past year or have taken weight-loss drugs in the past three months, and have lost more than 10% of their body weight; ⑨ have a history of drug or narcotic abuse; or ⑩ are pregnant and lactating or have major primary diseases or malignant tumours.

### Recruitment

Eligible participants will get basic information about this trial through outpatient physicians or the advertisements located in the hospital and communicate with investigators through contact details. Trained researchers will conduct investigations, obtain informed consent, and attending physicians will be responsible for the recruitment. Participants will be informed of the detailed procedures of the trial and shown the informed consent form after being verbally explained the possible benefits and potential risks to ensure that participation is entirely voluntary. Participants will have the option to proceed after signing the informed consent form. During enrolment, disease-related biological markers and imaging examinations will be performed, and the results will be confidentially recorded in the case report form (CRF).

### Study visit overview

Five visits including one follow-up are designed in this trial: at 6, 12, 18, 24, and 36 weeks after enrolment. Each time point has 5 days of time flexibility. Participants will have their vital signs checked at each visit, receive health education and medication for the next 6 weeks, and return any remaining drugs from the previous visit. Other concomitant medications and their doses during this period will be recorded in the CRF. Compliance with the treatment will be evaluated by pack count at each visit and serious adverse events will be recorded. MRI-PDFF examinations will be performed at weeks 0 and 24, and laboratory indicators will be measured at weeks 0, 12, and 24. SF-36, CLDQ, and TCMSSS will be filled out at 0 and 24 weeks. The TCMSSS consists of 55 questions about conventional symptoms of TCM syndromes, and each symptom is divided into four grades according to its frequency or degree. These questions are derived from a Patient-Reported Outcome (PRO) questionnaire for patients with hepatitis B virus-related cirrhosis (PHBC-PRO) [33, 34] and are expanded to studies of TCM for the treatment of chronic liver diseases. TCM syndrome diagnosis and its related degree can be reflected according to the combination and degree of positive symptoms. Any questions raised by participants will be answered to facilitate completion. The study schedule is shown in Fig. 2.

**Fig. 2 Fig2:**
[figure not shown]
Study schedule of enrolment, interventions, and assessments. Abbreviations: JPHX, Jian-Pi Huo-Xue granule; MRI-PDFF, magnetic resonance imaging - proton density fat fraction; BMI, body mass index; WHR, waist-to-hip ratio; TC, total cholesterol; TG, triglyceride; HDL-C, high-density lipoprotein cholesterol; LDL-C, low-density lipoprotein cholesterol; FPG, fasting plasma glucose; FINS, fasting insulin; HOMA-IR, homeostasis model assessment - insulin resistance; SF-36, Medical Outcomes Study item short-form health survey; CLDQ, Chronic Liver Disease Questionnaire; NAFLD, non-alcoholic fatty liver disease; TCM, traditional Chinese medicine

### Randomization and concealment

#### Allocation

Enrolled participants will be randomized 1:1 to either the JPHX group or the placebo control group according to a randomization sequence designed by an external statistician using SPSS software (Version 24.0). The sequence will be sealed in opaque envelopes and kept independently as confidential documents.

#### Blinding

All participants and investigators will be blinded to treatment assignments until the study is complete. Personnel unrelated to this trial will complete the preparation of drug blinding and emergency letters. The unblinding procedure will be performed twice. The first unblinding process will break down the assigned groups (Group A and Group B) without a specific intervention name. The statistician will perform statistical analysis without knowledge of the intervention. After analysis, a second unblinding will be conducted to reveal which group (Group A/Group B) is the treatment group/placebo group. All unblinding processes will be recorded. In case of emergency, we will record the reason, time, and place of breaking blindness and will treat it as a withdrawal case.

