### Interventions

Participants who met the inclusion criteria and signed an informed consent form will be randomly assigned to the JPXH group or the placebo-controlled group.

JPHX group: JPHX granules (6.39 g/pack × 2 packs, bid)

Placebo group: JPHX-placebo granules (2 packs, bid)

JPHX granules and placebo are recommended to be diluted in water and taken half an hour after meals. JPHX granules are composed of 8 kinds of Chinese herbs, including *Atractylodes macrocephala Koidz.* (Bai Zhu), *Salvia miltiorrhiza Bge.* (Dan Shen), *Citrus aurantium L.* (Zhi Qiao), *Paeonia lactiflora Pall.* (Bai Shao), *Pueraria lobata (Willd.) Ohwi* (Ge Gen), *Alisma orientalis (Sam.) Juzep.* (Ze Xie), *Schisandrae Chinensis Fructus.* (Wu Wei Zi), and *Curcuma Longa L.* (Jiang Huang) [19]. The placebo granules will be masked with the same packaging and similar taste compared to JPHX. Both JPHX and placebo are manufactured and packaged by Jiangyin Tianjiang Pharm Co., Ltd, Jiangyin city, Jiangsu, China.

Participants will receive regular health education, including diet control, exercise, and behaviour modification. ① Diet adjustment: diets with low-sugar, low-fat, and high-vitamin are recommended. ② Strengthen physical exercise: moderate-equivalent-intensity exercise, more than 30 min each time, 4 times a week. ③ Adjust mood and maintain a good mood; ④ During the trial, other TCM herbs and Western medicines mainly used to lower lipids or treat liver damage are prohibited.

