### Withdrawal, dropout, and discontinuation

Participants will be advised to discontinue participation in the event of a serious adverse event (SAE), or a condition during the course that does not meet the requirements of this trial, such as pregnancy or taking illicit drugs. There are no special criteria for modifying allocated interventions. Participants are free to withdraw at any time and the reason for withdrawal will be investigated. The reason and its connection with this trial will be recorded after investigation. If a moderate or severe adverse reaction determined to be related to the clinical trial occurs in more than 25% of the total participants, or if the required number of participants is not fully enrolled within the schedule, this clinical trial may be terminated.

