### Outcomes

The primary outcome is the relative change of MRI-PDFF from baseline to 24 weeks.

The secondary outcomes include changes in ① body weight, body mass index (BMI), waist-to-hip ratio (WHR); ② serum liver function including total bilirubin (TBIL), direct bilirubin (DBIL), indirect bilirubin (IDBIL), ALT, aspartate aminotransferase (AST) [16], gamma-glutamyl transpeptidase (GGT), alkaline phosphatase (ALP), albumin (ALB) [28], pre-albumin (Pre-ALB), and total bile acid (TBA); ③ fasting serum lipids; ④ blood glucose-related indicators, such as fasting plasma glucose (FPG), fasting insulin (FINS), and Homeostasis model assessment – insulin resistance (HOMA-IR). All mentioned serum biochemical markers will be measured at baseline, 12 weeks and 24 weeks after randomization. ⑤ Health related quality of life (SF-36). ⑥ Chronic Liver Disease Questionnaire (CLDQ), ⑦ TCM Syndrome Score Scale (TCMSSS).

Blood routine, urine routine, blood urea nitrogen, creatinine, uric acid, and SAEs are included as safety outcomes in this trial.

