### Statistical analysis

Statistical analysis will be performed by an independent researcher. The primary outcome efficacy evaluation will be conducted in the full analysis set [35] according to the intention-to-treatment (ITT) principle. Cases that met the trial protocol had good compliance (> 80%), did not take illicit drugs during the trial, and completed the contents of the CRF regulations will be defined as the Per-Protocol Set. The missing data will be replaced using the last observation carried forward (LOCF) method.

Continuous data will be described using mean ± standard deviation or median (range) depending on the distribution of the data. Comparison of mean or median values of continuous variables from the two groups will be undertaken using an independent *t* test or Wilcoxon rank-sum test. Paired *t* test or Wilcoxon signed-rank test will be used to compare the distribution of pre- and post-treatment changes within each group. Categorical data will be described by frequency counts and constituent ratio and will be compared using the chi-square test/Fisher exact test. All statistical analyses will be conducted with the bilateral test, and *P* value less than or equal to 0.05 will be considered statistically significant. Subgroup analyses will be performed based on information collected to explore the source of potential high heterogeneity.

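### The protocol ties leaving the trial to SAEs, non-qualifying conditions and code breaks and states no week-24 scan for these patients, so LOCF would enter an imputed zero change in the intention-to-treat analysis

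*Protocol article*

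**What the plan says.** All references are to the protocol article.

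- **Blinding.** On an emergency code break: "we will record the reason, time, and place of breaking blindness and will treat it as a withdrawal case".
- **Withdrawal, dropout, and discontinuation.** "Participants will be advised to discontinue participation in the event of a serious adverse event (SAE"). No condition on cause is attached. The same advice covers conditions that no longer fit the trial's requirements, "such as pregnancy or taking illicit drugs". Changes to the allocated intervention are dealt with in a separate sentence, so this advice concerns participation and not the granules alone.
- **Interventions.** During the trial "other TCM herbs and Western medicines mainly used to lower lipids or treat liver damage are prohibited". No consequence for participation is stated there.
- **Outcomes.** "The primary outcome is the relative change of MRI-PDFF from baseline to 24 weeks".
- **Study visit overview.** "MRI-PDFF examinations will be performed at weeks 0 and 24".
- **Statistical analysis.** "The primary outcome efficacy evaluation will be conducted in the full analysis set", on the intention-to-treat principle, with missing data replaced by LOCF. One condition for the per-protocol set is that the patient "did not take illicit drugs during the trial".

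**The concern.** Intention-to-treat needs outcome data on randomised patients whatever happens to their treatment. Here, events after randomisation lead to leaving the trial, and nothing in the article keeps the patient for the one post-baseline scan that the primary outcome needs. SAEs, code breaks and some drug use can plausibly depend on the assigned treatment or on prognosis. If they do, the missing scans are informative, and filling them with the baseline value can push the group comparison in either direction. The loss is also avoidable, because the week-24 assessments are already scheduled.

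**Working it through.** **1. What LOCF gives for an early leaver.** Scans are at weeks 0 and 24 only. Without the week-24 scan, the last observation is the baseline scan:

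relative change = (baseline − baseline) / baseline = 0%.

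This falls short of the 26% relative reduction used in Sample size justification, so the patient also counts as a non-responder. The SF-36, CLDQ and TCM syndrome scale are likewise completed only at weeks 0 and 24, so the same happens there. Laboratory tests also have a week-12 value to carry forward.

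**2. The sections side by side.** The per-protocol definition leaves out patients who took illicit drugs, which implies that they belong in the full analysis set. The withdrawal section advises the same patients to leave. The analysis therefore counts on patients whom the conduct rules steer out before their outcome is measured.

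**3. Illustration on the mean scale.** The article gives no rates of SAEs, code breaks or drug use. Assumptions, none of them from the document: no drug effect; a mean improvement *m* of 20% to 30% in both arms; 5 early leavers in one arm and 1 in the other; leavers would have improved as much as the rest; all 42 per arm are in the full analysis set.

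- Arm with 5 leavers: mean = *m* × 37/42, that is 17.6 (*m* = 20) or 26.4 (*m* = 30).
- Arm with 1 leaver: mean = *m* × 41/42, that is 19.5 or 29.3.
- Spurious difference = *m* × (5 − 1)/42 = 1.9 (*m* = 20) to 2.9 (*m* = 30) percentage points, against the arm with more leavers.

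Each leaver is 1/42 = 2.4% of an arm.

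**4. The plan's own sample size.** The printed formula uses the one-sided z for α = 0.05, with β = 0.2, rates of 0.6 and 0.3, and δ = 0.01:

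n = (1.645 + 0.842)² × (0.24 + 0.21) / (0.30 − 0.01)² = 33.08.

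The article states 33. Then 33/0.8 = 41.25, rounded up to the stated 42 per group.

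**5. Illustration on the responder scale.** Each early leaver counts as a non-responder, so the expected rate in an arm is the planned rate × (1 − loss). Power is for two proportions, 42 per arm, two-sided 0.05. The 20% is the plan's overall dropout figure; the other loss rates are assumptions.

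| Loss JPHX / placebo | Response rates | Difference | Power |
|---|---|---|---|
| 0% / 0% | 0.60 vs 0.30 | 0.30 | 80% |
| 10% / 10% | 0.54 vs 0.27 | 0.27 | 72% |
| 20% / 20% | 0.48 vs 0.24 | 0.24 | 63% |
| 20% / 10% | 0.48 vs 0.27 | 0.21 | 51% |
| 10% / 20% | 0.54 vs 0.24 | 0.30 | 82% |

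These losses cover dropout of every kind. The rules discussed here would cause an unknown share of it. The table shows that equal loss shrinks the difference, and that unequal loss moves it down or up relative to equal loss.

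**The case against.** The strongest reply is that the article does not say that scans stop. Treating a code break as a withdrawal case may be a classification and not an order to end assessments. The full protocol (version 1.0) is not shown, nor is the schedule figure, and either could provide for assessment after discontinuation. This stands in part: loss of the scan is an inference. It is still the natural reading of the two sections, and if the full protocol does retain these patients, the published wording misdescribes it.

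Several stronger readings are tempting, and the document does not support them:

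- **That the intention-to-treat analysis cannot be done.** It can, because LOCF supplies a value. The problem is what that value is.
- **That every SAE removes the patient.** Patients are advised to leave, not compelled.
- **That use of the banned lipid or liver medicines leads to withdrawal.** The withdrawal section speaks of illicit drugs. Its general clause on trial requirements may cover the medicines banned under Interventions, but the article does not make the link.
- **That scans are lost for treatment-related reasons.** This is possible but not shown, since no event rates are given.
- **That safety follow-up ends.** Nothing says so. The abstract has adverse events managed and recorded promptly, and reasons for withdrawal are to be investigated.
- **That such losses use up the dropout allowance.** In the illustration they are 6/84 = 7.1% overall and 5/42 = 11.9% in the worse arm, both below 20%.

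It is also fair to say that part of the harm comes from LOCF with only two scans, which would affect any dropout. What is specific here is that the plan's own rules add to the dropout.

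**Conclusion.** The point holds in limited form. The withdrawal and blinding sections link events after randomisation to leaving the trial, not merely to stopping granules, and state no week-24 scan for those patients. With scans only at weeks 0 and 24, an early leaver enters the full analysis set as an imputed 0% change. This is at odds with the intention-to-treat principle that the analysis section adopts.

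The size cannot be fixed from the document. The 1.9–2.9 points rest on an assumed 5-versus-1 split and an assumed 20–30% mean improvement in both arms. The fall in power to 63% rests on the full 20% loss in each arm being scored as non-response. The bias can go either way, and it arises only if the events differ between arms or depend on prognosis. The conclusion also assumes that leaving means no week-24 scan. This is a worthwhile, inexpensive improvement and not a flaw that invalidates the trial.

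**What to change.** Reconcile the withdrawal and blinding sections with the analysis section in one paragraph:

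- Separate the end of study treatment, or a code break, from the end of data collection.
- Unless consent is withdrawn, keep these patients for the scheduled week-24 MRI-PDFF (where it can be done), laboratory tests and adverse-event follow-up.
- Analyse them as randomised in the full analysis set, and confine exclusions to the per-protocol set.
- Say whether illicit drugs means the co-medication banned under Interventions.

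The rules on when granules are stopped stay as they are. The cost is a protocol amendment with ethics re-approval, as Ethical consideration requires, and already scheduled assessments for a few more patients. The estimates will then include data collected off treatment, which is what intention-to-treat intends.

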### Ethical consideration

The clinical trial was approved by the Ethics Committee of Shuguang Hospital (Ethics approval number: 2021-934-09-01) on January 27, 2021. If the protocol is modified during the trial, it needs to be re-approved by the ethics committee before implementation. The process of this trial will follow the ethical regulations of the Declaration of Helsinki and will be monitored by the Institutional Review Board (IRB) of Shuguang Hospital affiliated with Shanghai University of TCM and the Science and Technology Commission of Shanghai Municipality.

### Data management

All collected data will be managed by an Electronic Data Capture (EDC) system program compiled by the Information Technology Department in Shuguang Hospital. Data will be entered and proofread independently by two data administrators. Locked data files will not be changed. Problems found after data locking will be corrected in the statistical analysis state after confirmation. Participant data will be anonymized and all data collected will be kept confidential in this trial.

### Data monitoring and Steering committee

The principal investigators will supervise correct development of the trial. The data monitoring committee of the Clinical Research Center of Shuguang Hospital and the Science and Technology Commission of Shanghai Municipality oversee the trial. The results of this trial will be submitted for publication in peer-reviewed journals and can be disseminated through conference presentations.

### Statistical analysis

Statistical analysis will be performed by an independent researcher. The primary outcome efficacy evaluation will be conducted in the full analysis set [35] according to the intention-to-treatment (ITT) principle. Cases that met the trial protocol had good compliance (> 80%), did not take illicit drugs during the trial, and completed the contents of the CRF regulations will be defined as the Per-Protocol Set. The missing data will be replaced using the last observation carried forward (LOCF) method.

Continuous data will be described using mean ± standard deviation or median (range) depending on the distribution of the data. Comparison of mean or median values of continuous variables from the two groups will be undertaken using an independent *t* test or Wilcoxon rank-sum test. Paired *t* test or Wilcoxon signed-rank test will be used to compare the distribution of pre- and post-treatment changes within each group. Categorical data will be described by frequency counts and constituent ratio and will be compared using the chi-square test/Fisher exact test. All statistical analyses will be conducted with the bilateral test, and *P* value less than or equal to 0.05 will be considered statistically significant. Subgroup analyses will be performed based on information collected to explore the source of potential high heterogeneity.

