### Sample size justification

A previous pilot trial in Shuguang Hospital used comprehensive scores of abdominal ultrasounds to evaluate efficacy. The score includes the evaluation of 7 indicators such as liver shape, contour, echo, and vascular structure. Each indicator is divided into 4 grades: normal, mild, moderate, and severely abnormal. Twenty-six patients (65%) experienced a 1-grade or more decrease in at least 3 indicators after treatment with JPHX compared to baseline [27, 29]. In this trial, a 26% relative reduction from baseline in liver MRI-PDFF will be expected in 60% of JPHX-treated cases compared to 30% in the placebo control group. Assuming *α* = 0.05, *β* = 0.2, *π*_*T*_ = 0.6, *π*_*C*_ = 0.3, *δ* = 0.01, *n*_*T*_ : *n*_*C*_ = 1:1. According to the optimal sample size calculation formula, each group will get 33 samples. Considering the dropout rate of 20%, a minimum of 42 individuals will be obtained per group.$${\mathrm{n}}_{\mathrm{T}}={\mathrm{n}}_{\mathrm{C}}=\frac{{\left({z}_{1-\alpha }+{z}_{1-\beta}\right)}^2\left[{\pi}_T\left(1-{\pi}_T\right)+{\pi}_C\left(1-{\pi}_C\right)\right]}{{\left[\left({\pi}_T-{\pi}_C\right)-\delta \right]}^2}$$

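### LOCF is fixed for missing data, but MRI-PDFF is scanned only at weeks 0 and 24, so a missing week-24 scan becomes 0% change and biases the primary comparison

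*Protocol article*

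**What the plan says.** Four statements in the protocol article meet on this point.

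- **Outcomes:** "The primary outcome is the relative change of MRI-PDFF from baseline to 24 weeks".
- **Study visit overview:** "MRI-PDFF examinations will be performed at weeks 0 and 24, and laboratory indicators will be measured at weeks 0, 12, and 24". The same two time points, baseline and week 24, apply to TCMSSS, CLDQ and SF-36.
- **Statistical analysis:** "The primary outcome efficacy evaluation will be conducted in the full analysis set [35] according to the intention-to-treatment (ITT) principle". Then, with no outcome exempted: "The missing data will be replaced using the last observation carried forward (LOCF) method".
- **Sample size justification:** a 26% relative reduction "will be expected in 60% of JPHX-treated cases compared to 30% in the placebo control group". Also: "Considering the dropout rate of 20%, a minimum of 42 individuals will be obtained per group".

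The article gives no other method and no sensitivity analysis for a missing primary outcome. It defines a per-protocol set but does not define the full analysis set further.

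**The concern.** LOCF needs an observation between baseline and the endpoint if it is to say anything about the course under treatment. The laboratory markers have one at week 12. MRI-PDFF does not, so LOCF becomes baseline carried forward: the relative change is (baseline − baseline)/baseline = 0%, and the 26% criterion is not met.

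Zero is not a neutral value in this trial. Both arms receive diet and exercise education, and the sizing itself assumes that 30% of placebo participants reach a 26% relative reduction. A participant without a scan is thus given a result that the plan does not expect, on average, in either arm.

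Two things are at stake. With equal dropout, the estimated effect is pulled toward zero. The sample size does not allow for this, because moving from 33 to 42 per arm treats dropouts as absent, whereas the stated analysis counts them as unchanged. With unequal dropout, the arm that keeps more participants looks better for that reason alone, so the method cannot be relied on to be conservative.

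**Working it through.** **Inputs from the protocol article:** response 60% v 30%; α = 0.05, β = 0.2, δ = 0.01; 33 evaluable and 42 randomised per arm; 20% dropout; two-sided testing. **Assumptions:** dropout is unrelated to outcome; for the mean comparison, relative change is normal with a common SD of 20 to 35 points. The unequal dropout rates in step 4 are hypothetical.

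**1. The plan's own figure.** The stated formula uses z(1−α), which is one-sided:

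n = (1.645 + 0.842)² × [0.6×0.4 + 0.3×0.7] / (0.30 − 0.01)² = 33.08, reported as 33. Then 33/0.8 = 41.25, rounded up to 42. It reproduces.

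**2. Responder scale, 20% missing in each arm.** About 8 of 42 per arm (0.2 × 42 = 8.4) are set to non-response.

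- JPHX: 0.8 × 60% = 48%. Placebo: 0.8 × 30% = 24%. The difference falls from 30 to 24 points.
- Power = Φ{[(p₁ − p₂) − z·SE₀]/SE₁}, with SE₀ pooled and SE₁ unpooled.

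| Case | Two-sided | One-sided |
|---|---|---|
| 42 per arm, no missing data, 60% v 30% | 80.0% | 88.0% |
| 33 completers per arm, 60% v 30% | 69.6% | 80.1% |
| 42 per arm, baseline carried forward, 48% v 24% | 63.4% | 74.8% |

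Against completers, LOCF costs about 6 points two-sided (69.6 − 63.4). The other 10 or so points below 80% are there without any imputation. They arise because the sizing was one-sided and the tests are two-sided.

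**3. Continuous outcome, 20% missing in each arm.** Means are set so that 60% and 30% pass a 26% reduction. At SD 30:

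- JPHX: −26 − 0.253×30 = −33.6. Placebo: −26 + 0.524×30 = −10.3. True difference: −23.3.
- With a fraction q set to zero, the mean is (1−q)m and the variance is (1−q)s² + q(1−q)m². At q = 0.2 the difference is 0.8 × (−23.3) = −18.7. The variances are about 901 and 737, and SE = √[(901 + 737)/42] = 6.24.
- Normal-approximation power: Φ(18.7/6.24 − 1.96) ≈ 85%. Completers (33.6 per arm): SE = 30√(2/33.6) = 7.32, power Φ(23.3/7.32 − 1.96) ≈ 89%.

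Simulated t tests give slightly lower values:

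| SD | True difference | With LOCF | Power, LOCF | Power, completers |
|---|---|---|---|---|
| 20 | −15.6 | −12.4 | 79% | 88% |
| 30 | −23.3 | −18.7 | 84% | 88% |
| 35 | −27.2 | −21.8 | 85% | 88% |

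**4. Unequal dropout (hypothetical).**

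- *True effect as planned, SD 30.* Dropout of 30% JPHX/10% placebo: 0.7×(−33.6) − 0.9×(−10.3) = −14.3. The reverse, 10%/30%: −23.1, almost unbiased. At SD 20 the reverse case gives −17.1 against a true −15.6, so the effect is exaggerated.
- *No effect, both arms at 30% response, dropout 10%/30%, mean scale.* The spurious difference is (0.9 − 0.7) × |mean|: 0.2×15.5 = 3.1 points (SD 20), 0.2×10.3 = 2.1 (SD 30), 0.2×7.6 = 1.5 (SD 35). Simulated two-sided type I error is about 12%, 7% and 6%. The completer analysis stays near 5%.
- *The same null case, responder scale.* 0.9×30% = 27% v 0.7×30% = 21%, a spurious 6 points, with type I error 9.8%.

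**The case against.** Several points on the other side are sound.

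- **Attribution of the power loss.** A reader might infer that LOCF alone takes the trial from 80% to 63%. It does not; most of that gap is the one-sided sizing.
- **The scale.** The primary outcome as defined is continuous. On that scale, with equal 20% dropout, power stays at about 79-85%, so the loss against completers is modest. The 20% shrinkage of the estimate remains.
- **Imbalance.** Nothing in this double-blind protocol suggests threefold unequal dropout. With 15%/25%, calibrated type I error is only about 5-7% on the mean scale. A reader might reach 10-16% by letting both arms improve by 20 points at SD 30 or 20, but that implies 42% or 38% responders, Φ(−6/30) or Φ(−6/20), not the plan's 30%.
- **Standard errors.** Treating imputed zeros as data might be expected to upset the test in itself. With equal dropout and no effect, simulated rejection stays at about 5%, so this is not a separate harm to the error rate.
- **Who is imputed.** It is tempting to say that every dropout is scored as zero. The text supports less: a participant who stops treatment may still be scanned. If the full analysis set required a post-baseline scan, LOCF would impute no primary values and the analysis would be completers only. The article does not say so, and that would sit badly with its stated ITT principle.
- **The test.** The article also allows a Wilcoxon test, so the t-test figures are illustrative.

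These points reduce the size of the problem. They do not remove the conflict between the imputation rule and the scan schedule.

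**Conclusion.** The point holds. As written, LOCF gives every participant in the full analysis set without a week-24 scan 0% change and non-response on the primary outcome. SF-36, CLDQ and TCMSSS share the problem.

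At the planned 20% dropout, if equal and unrelated to outcome, the treatment difference is understated by a fifth on either scale. LOCF itself costs about 6 points of two-sided responder power, and about 3 to 9 points on the continuous outcome, depending on the assumed SD.

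The claim that LOCF is not reliably conservative rests on hypothetical unequal dropout. In that case bias can run in either direction, with type I error of about 6-12% on the mean scale at a 10%/30% split. Only the 20% dropout and the 60%/30% response rates come from the document; normality, the SDs, random dropout and the imbalance are assumptions.

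**What to change.** Replace LOCF as the primary missing-data method for MRI-PDFF with an analysis valid under missing at random. One suitable choice is multiple imputation of week-24 MRI-PDFF from arm, baseline MRI-PDFF and a small prespecified set of week-12 measurements already collected, such as ALT. Week-24 auxiliaries can be used where available, but they will often be missing for the same participants. With about 33 completers per arm, the model should stay small and not take in every laboratory marker.

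Keep baseline carried forward as a sensitivity analysis, beside a delta-adjusted or placebo-based imputation. State whether the full analysis set includes participants without a week-24 scan, and give a method other than LOCF for SF-36, CLDQ and TCMSSS.

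The change should be fixed before the groups are unblinded. It costs analysis wording and a little programming, and needs no new data.
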